# Group Acceptance and Commitment Therapy for Recovery From Psychosis: Protocol for a Single-Group Waitlist Trial

**DOI:** 10.2196/49849

**Published:** 2024-03-18

**Keywords:** Acceptance and Commitment Therapy, ACT, group therapy, interventions, personal recovery, protocol, psychosis, psychotic disorders, public mental health services

## Abstract

**Background:**

Psychological interventions, along with antipsychotic medications, are recommended for adults diagnosed with a psychotic disorder. While initially designed to mitigate positive symptoms, psychological interventions targeting personal recovery were developed and aligned with the recovery framework that many mental health services have adopted. Acceptance and Commitment Therapy (ACT) for psychosis is one such intervention that shows promise when delivered in an individual format. There is preliminary evidence that ACT for psychosis in a group format improves recovery.

**Objective:**

This trial aims to evaluate the effectiveness of the “Recovery ACT” group program on personal recovery among adults living with a psychotic disorder.

**Methods:**

Our unfunded study is a multiagency, prospective, nonrandomized, waitlist control, single-group trial of the Recovery ACT group program. The program involves 7 weekly group sessions of 90 minutes duration and a 90-minute booster session held 1 month later. We intend to recruit 160 adults living with a psychotic disorder who enroll in a group that is offered as a routine clinical service at participating public mental health services in Melbourne, Victoria, Australia. The 4 assessment time points are 4-6 weeks before the start of the group program, at the start of the group program, at the end of the group program, and at the booster session. There is an optional midgroup assessment and follow-up study. The primary outcome is personal recovery. Secondary outcomes include participants’ well-being and psychological flexibility processes. Qualitative data are also collected from participants and facilitators.

**Results:**

Recruitment began in September 2019 and is ongoing until 2024, subsequent to a 24-month disruption due to the COVID-19 pandemic. As of the submission of this paper, 93 participants consented to the evaluation, 65 completed T1 measures, and 40 had a complete data set for the proposed analyses.

**Conclusions:**

This is the first trial evaluating the effectiveness of the Recovery ACT group program on personal recovery for adults living with a psychotic disorder. Findings will contribute to knowledge about psychosocial interventions for adults living with psychosis. This trial may also serve as an example of a partnership between clinicians and academics that can facilitate the translation of research into practice.

**Trial Registration:**

Australian New Zealand Clinical Trials Registry ACTRN12620000223932; https://anzctr.org.au/Trial/Registration/TrialReview.aspx?ACTRN=12620000223932

**International Registered Report Identifier (IRRID):**

DERR1-10.2196/49849

## Introduction

### Background and Rationale

Schizophrenia spectrum disorders have a prevalence rate of 3.3 per 1000 individuals worldwide [1], with schizophrenia ranking as the twelfth most disabling disorder [2]. Psychotic disorders are typically first diagnosed in young adulthood and can run a chronic course [3]. About two-thirds of individuals diagnosed with a psychotic disorder continue to experience persistent psychotic symptoms despite adhering to antipsychotic medication regimens; about 20% do not respond at all [4]. In addition, there is a high prevalence of comorbid anxiety and mood disorders—about 40% experience anxiety [5,6] and 30%-80% experience depression [6,7]—and other challenges (eg, stigma and social exclusion) that impact well-being and functioning. Persisting psychotic symptoms, comorbid anxiety and depression, and other challenges not only contribute to an individual’s level of distress and functioning but also impact a person’s ability to fully engage in life [8], referred to as personal recovery [9].

For over 2 decades, psychological and psychosocial interventions have been internationally recommended as adjuncts to pharmacological interventions [10-13]. The leading evidence-based psychological intervention recommended for psychotic disorders is cognitive behavioral therapy for psychosis (CBTp). This intervention involves teaching skills to modify unhelpful thinking patterns that impact behavior [14] and primarily targets reduction in psychotic symptoms and, arguably, distress and functioning as well. While meta-analyses demonstrate that CBTp reduces psychotic symptoms (most notably positive symptoms) with a small effect size [15-17], CBTp does not appear to mitigate distress or improve quality of life [18]. The latter findings continue to be challenged [19,20]. Modifications of CBTp (eg, low-intensity CBTp [21,22] and group CBTp [23]) are promising, though they have yet to amass robust evidence to be recommended in treatment guidelines.

Another promising psychological therapy for psychotic disorders is Acceptance and Commitment Therapy (ACT). This approach involves developing psychological flexibility, which is the ability to be in conscious contact with the present moment, and the capacity to persist with or change behavior based on whether it aligns with one's personal values [24]. Psychological flexibility processes include willingness to be with mental experiences (thoughts, feelings, sensations, etc) instead of engaging in experiential avoidance; cognitive defusion (distancing or observing with openness and curiosity) with mental experiences; engagement in valued actions; and mindfulness (ie, awareness of the present moment) [24]. ACT adapted for individuals living with a psychotic disorder has been implemented in both inpatient and outpatient settings. There is emerging evidence [25] that this intervention not only reduces rehospitalization [26-28] but can also improve quality of life and personal recovery [29].

The first ACT for psychosis group intervention targeting quality of life and social functioning was a 4-session group (2-hour sessions run weekly) known as the “ACT for Life” program, a manualized protocol developed by researchers in the United Kingdom for adults living with psychosis [30,31]. An initial uncontrolled study evaluating this program at a community psychosis service in the United Kingdom [32] demonstrated small improvements in functioning and mood after group completion. A subsequent controlled study [33] demonstrated the positive effects of group participation on well-being over time and greater independence, as indicated by service use changes. Both studies demonstrated that the group was feasible and acceptable to adults living with psychosis.

Building on promising results from individual and group ACT programs for psychosis, the ACT for Life program was adapted for public outpatient mental health services in Melbourne, Victoria, Australia [34]. A pilot of the adapted program, referred to as “Recovery ACT,” was implemented by public mental health service clinicians as part of their routine practice and evaluated using pre- and postgroup outcome measures together with qualitative feedback from facilitators and participating consumers [35]. Results from the uncontrolled pilot study involving 9 groups and 90 consumers demonstrated that the program and its evaluation were feasible, acceptable, and safe [35]. Significant increases in personal recovery, well-being, and psychological flexibility were observed from the start to the end of the program. The extent of consumer and clinician interest in the groups, both from the original agency and additional agencies, strongly indicated the feasibility of conducting a more extensive evaluation. Building on this momentum, our clinician-academic partnership agreed to conduct this more stringent trial by incorporating a waitlist control period and an established measure of personal recovery as the primary outcome.

### Objectives

The primary aim is to evaluate the effectiveness of the Recovery ACT group program on personal recovery for adults living with a psychotic disorder in routine clinical practice across public mental health organizations in Australia using a single-group, waitlist control design. A secondary aim is to evaluate the effect of the Recovery ACT group program on well-being and psychological flexibility processes (experiential avoidance, cognitive defusion, engagement in valued actions, and mindfulness). The research questions are as follows: (1) What are the clinical benefits and risks of the Recovery ACT group program for adults diagnosed with psychotic disorders as conducted in routine practice in Australia? (2) Are there changes in psychological flexibility processes due to participation in the Recovery ACT group program? (3) Are changes in psychological flexibility processes associated with changes in personal recovery and well-being?

The primary and secondary hypotheses are that the longitudinal trajectory of personal recovery and the secondary outcomes will not significantly change over the waitlist period, then will improve from the start to the end of the group program, and then improve at a less rapid rate from the end of the group to the booster session. A further hypothesis is that changes in psychological flexibility processes during the first half of the group program will be associated with changes in personal recovery and well-being in the second half of the group program.

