### Outcomes

#### Timeline

The schedule of enrollment, interventions, and assessments is displayed in Figure 2. The quantitative self-report outcome measures are intended to be completed independently at the start of the waitlist period (T0, approximately 4-6 weeks before the start of the group program, typically at the “Information and Engagement” session), at the start of the group program (T1), at the end of the group program (T3, which is 6 weeks after the start of the group program), and at the booster session (T4, about 10 weeks after the start of the group program). Some participants may complete outcome measures at the midpoint session (T2, which is 3 weeks after the start of the group program) if the study site is resourced to collect data at an additional time point. Measures are completed after the group session, except for at T1, when participants complete measures before the start of the group to ensure no exposure to the program’s content. Participants can request assistance from facilitators to complete the measures. Demographic and clinical information will be obtained from participants’ electronic health records at T0 and will include their date of birth, gender, ethnicity, country of birth, highest level of educational attainment, highest level of employment, current employment status, primary mental health file diagnosis, co-occurring mental health file diagnoses, date of first contact with mental health services, number of listed episodes of outpatient mental health care, and number of psychiatric admissions.

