### Statistical Methods and Sample Size

We intend to use an intention-to-treat sample to test a univariate latent growth curve model of the primary outcome from before the start of the waitlist period to the start of the group to the booster session in order to compare the trajectory over the waitlist period to the trajectory over the active treatment period. We selected this method of analysis to strengthen our estimations of associations due to the limitations of the nonrandomized study design chosen as the most realistic option for an evaluation of a program already in routine practice [51]. A minimum sample size of 90 is required to conduct the proposed growth curve structural equation model (5 observed variables and 2 latent variables) with an anticipated medium effect size (0.3), α set at .05, and power (1–β) at .80. Univariate latent growth curve models for each of the 5 secondary outcomes will also be tested. If there are sufficient data, we will test whether the trajectory of the 4 psychological flexibility process variables from the start of the group to the midpoint session (T1 to T2) is significantly associated with the trajectory of personal recovery (T2 to T4) using multivariate growth models. We do not predict a priori any differences associated with the study site. We intend to calculate the ICC after the data are collected to determine the relatedness of the data collected at different study sites.

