#### Randomization and Blinding

This study is a nonrandomized (unblinded) trial that uses a single group, waitlist control, and a quasiexperimental design. All participants serve as their own control. The data for all participants on change in outcomes over the waitlist period (no active intervention) will be used to compare with the data on change in outcomes during the active intervention. The planned statistical methods will strengthen our conclusions. The risk of researcher bias is lessened by the self-report format of the primary and secondary outcomes and the opportunity for participants to submit questionnaires in a sealed envelope.

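### The primary hypothesis is worded as a pattern that never requires the group-period gain to exceed the waitlist change, while the methods promise that comparison; as worded, steady drift could satisfy it

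*Protocol article*

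**What the plan says.** The Objectives section of the protocol article gives one hypothesis for the primary and secondary outcomes, in three limbs. For the first two, the outcome "will not significantly change over the waitlist period, then will improve from the start to the end of the group program". The third limb predicts a slower gain after the group has finished, up to the booster. Each limb describes one interval. None says that change over the group period is larger than change over the wait.

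The methods are framed differently. Statistical Methods and Sample Size says a latent growth curve model will be tested "in order to compare the trajectory over the waitlist period to the trajectory over the active treatment period". Randomization and Blinding says all participants are their own controls and that waitlist change "will be used to compare with the data on change in outcomes during the active intervention". Neither section names the parameter that carries the comparison. The model is described as having five observed and two latent variables. The minimum sample of 90 is justified "with an anticipated medium effect size (0.3), α set at .05", and "power (1–β) at .80".

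The first assessment is "approximately 4-6 weeks before the start of the group program"; the group period is about 6 weeks (Study Design, Timeline).

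**The concern.** A non-significant waitlist change is not evidence of no change. A significant change in one period beside a non-significant change in another does not show that the two differ. The waitlist is the only control in this single-group design, and the only question it can answer is whether improvement sped up once the group began. The hypothesis as worded does not ask that.

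Two features of the design add to the problem. The wait may be shorter than the group period, so a constant weekly drift produces a smaller and less often significant waitlist change. T1 also enters both changes, so a chance-low T1 flattens the wait and enlarges the group gain. Natural improvement at an unchanged rate, in patients whose other care is unrestricted (Intervention), could then be credited to the program.

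**Working it through.** **Inputs.** From the article: n=90, alpha .05 (taken as two-sided), effect 0.3, power .80, wait 4-6 weeks, group period 6 weeks, QPR test-retest ICC 0.74. Assumed: independent errors around a stable person level, with variance 1 - 0.74 = 0.26 in QPR SD units; a constant drift d (SD per 6 weeks) through all periods; program effect zero. The documents give no drift, so a range is shown.

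**The plan's own figure.** The normal approximation for one paired change is (1.96 + 0.8416)² / 0.3² = 87.2, so 88; the exact paired t-test gives 90. A structural-equation lower bound for an effect of 0.3 gives 89.1, so 90. The stated 90 therefore reproduces, for a generic effect of 0.3 or a single paired change. Recruitment covers it: 90 / 0.60 = 150, and 160 × 0.60 = 96.

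**Pattern with no program effect.** Each change has SD √(2 × 0.26) = 0.721. For a wait of w weeks:

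- waitlist test mean = (d·w/6) / 0.721 × √90
- group test mean = d / 0.721 × √90
- correlation between the two changes = -0.5, because they share T1

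Example, d = 0.15, w = 5: the means are 0.125 / 0.721 × 9.487 = 1.64 and 0.15 / 0.721 × 9.487 = 1.97. The waitlist test is non-significant with probability 0.62 and the group test significant with probability 0.51. With correlation -0.5, both happen with probability 0.39.

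Simulated across waits of 4 to 6 weeks:

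| Drift, SD per 6 weeks | Limbs 1 and 2 both met |
|---|---|
| 0 | about 2% |
| 0.05 | 9-10% |
| 0.10 | 23-24% |
| 0.15 | 32-43% |
| 0.20 | 24-49% |
| 0.40 | 0-7% |

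With the third limb added as a lower point slope from T3 to T4, the range at 0.15-0.20 is 16-35%. The peak over all drifts (33%, 41% and 51% for waits of 6, 5 and 4 weeks) is the same at n = 40, 96 and 160; only the drift at which it occurs moves. More recruitment does not remove it.

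**Direct contrast.** C = (T3 - T1)/6 - (T1 - T0)/w. With no program effect, its test favours the program in 2-3% of trials at every drift, as a two-sided 5% test should.

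**Power of the contrast.** For a true effect of dz 0.3 on T1-T3, the mean of C is 0.3 × 0.721 / 6 = 0.0361, and Var(C) = 0.26 × [1/36 + (1/6 + 1/w)² + 1/w²].

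| Wait (weeks) | SD of C | 0.0361/SD × √90 | Power, normal approximation | Completers for 80% |
|---|---|---|---|---|
| 4 | 0.262 | 1.31 | 26% | 415 |
| 5 | 0.229 | 1.49 | 32% | 318 |
| 6 | 0.208 | 1.64 | 38% | 262 |

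The t-test is slightly lower, about 25-37%.

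**The case against.** A reader might infer that the protocol will declare success when the waitlist test is non-significant and the group test is significant. It does not say so. The Objectives state an expected trajectory, no section gives a success rule, and two methods sections say the periods will be compared, which is the remedy in principle. Naming the model parameter could be left to a full protocol or analysis plan that is not shown. This stands, and it limits the point to a mismatch between the hypothesis and the methods. It does not remove the mismatch, because the hypothesis wording is fixed in this article. Two latent variables, if they are the usual intercept and one slope, also do not evidently provide separate waitlist and treatment slopes. A model with freed loadings might, but the article does not describe one.

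A reader might also infer that false success would be frequent in general. That is not supported. With no drift the rate is about 2%, and with strong drift the waitlist limb fails. Drift of 0.15-0.20 SD per 6 weeks would be 1.3-1.7 SD over a year if sustained, which is a lot in a condition the article calls potentially chronic. Drift over a few weeks need not last a year, however, and 0.05-0.10 SD already gives 9-24% on the first two limbs.

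The third limb gives real protection. If it also requires a positive T3-T4 change, the rate is about 2.6% at 0.05 SD, 12-13% at 0.10 and 14-31% at 0.15-0.20.

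Finally, the waitlist range includes 6 weeks, so unequal intervals are not certain; the table shows that the problem persists at 6 weeks. T1 enters the contrast too, but there its error is counted in the standard error.

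**Conclusion.** The point holds as a need to reconcile the hypothesis with the methods. The hypothesis makes a non-significant waitlist change part of the predicted result and omits the comparison that the methods describe. If the hypothesis as worded were used to judge the trial, modest constant drift and no program effect would meet its first two limbs in roughly 9-49% of trials at drifts of 0.05-0.20 SD per 6 weeks, against 2-3% for the direct contrast. These figures rest on n=90, independent errors with variance 0.26, and an assumed drift.

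The wording can also count against the program. With a true effect of dz 0.3 and a 5-week wait, the two-limb pattern is met in 77% of trials with no drift but in only 35% when drift over the group period is dz 0.3, because the waitlist change then becomes significant.

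The stated 80% power fits a single paired change of dz 0.3. It does not carry over to the contrast that the methods imply.

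**What to change.** In Objectives, state the primary hypothesis as one test: weekly QPR change from T1 to T3 minus weekly change from T0 to T1 is greater than 0, using actual assessment dates. In Statistical Methods, name that contrast as the primary test, within a growth model that has separate waitlist and treatment slopes. Report the waitlist slope with its 95% CI as description, not as a condition. Use the same form for the five secondary outcomes. The slower improvement to the booster can stay as a further, descriptive prediction.

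The change costs wording, a revised model specification and entry of assessment dates. The article reports that no data analysis has been conducted, so it can still be made in advance.

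The real price is power and should be disclosed: about 25-37% at 90 completers for waits of 4-6 weeks, with 262-415 completers needed for 80%. The article reports 40 complete data sets against a target of 160 recruits in an unfunded trial. The 80% claim should therefore not be attached to the contrast, and its estimate and interval should be reported with that limit stated.

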## Methods

### Participants and Study Setting

We plan to recruit a minimum of 160 adults (aged between 18 and 65 years) who enroll in a Recovery ACT group program at 1 of 4 public mental health service study sites in Melbourne (NorthWestern Mental Health, St Vincent’s Mental Health Service, Alfred Mental and Addiction Health, and Peninsula Health Mental Health Service). The target minimum number of participants at NorthWestern Mental Health is 95 participants, and 32 participants each at the other study sites. The overall recruitment target was based on the minimum sample size needed to complete the intended analyses and an anticipated 60% participant retention rate based on the pilot study [35].

The inclusion criteria are a primary file diagnosis of either schizophrenia spectrum disorder or other psychotic disorder, a mood disorder with psychotic features, or a substance-induced psychotic disorder; currently receiving outpatient mental health care at 1 of the study sites; and current enrollment in a Recovery ACT group program. The exclusion criteria are lack of capacity to consent to the evaluation; lack of proficiency in speaking and comprehending English; a file diagnosis of intellectual disability or borderline personality disorder.

### Study Design

This trial is a multiagency, prospective, longitudinal, nonrandomized, waitlist control, single-group study among Australian adults diagnosed with a psychotic disorder who participate in a routine Recovery ACT group program. The design includes 4 assessment time points: the start of the waitlist period (approximately 4-6 weeks before the start of the group program), the start of the group program (0 weeks), the end of the group program (about 6 weeks after the start of the group program), and the booster session (about 10 weeks after the start of the group program). Some participants may complete outcome measures at the midpoint session (T2, which is 3 weeks after the start of the group program) if the study site is resourced to collect data at an additional time point. Quantitative data from facilitators about participants’ clinical severity and clinical improvement will be collected before, during, and after the group program, as well as relevant demographic and clinical information collected at baseline from participants’ electronic medical records. At either the end of session 7 or the booster session, participants will be asked to provide written consent for study personnel to contact them for a follow-up study. Facilitators will be invited to complete a semistructured interview with senior investigators after each group program to gather qualitative data about the feasibility of the group program in routine practice and to assist in the interpretation of the quantitative measures completed by participants. The protocol development addressed the SPIRIT (Standard Protocol Items: Recommendations for Interventional Trials; Multimedia Appendix 1) guidelines [36] and intends to adhere to the CONSORT (Consolidated Standards of Reporting Trials; Figure 1) criteria [37]. We retrospectively registered the trial with the Australian New Zealand Clinical Trials Registry; Table 1 lists the trial registration data set.

